#### Objectives

1. To identify the barriers and facilitators for major system reconfiguration, implementation, and sustainability.

2. To study whether the reconfigurations have delivered clinical and cost effective improvements that patients and public think are worthwhile.

3. To identify lessons about major service reconfiguration that might be applied in other settings (i.e. other locations and other service domains).

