### Data collection

#### Understanding what works and at what cost

To establish what models were applied and how they were developed and put into action in London and Greater Manchester, the evaluation will analyse a range of documentary evidence. This will include project board papers, service designation criteria, and tariff documentation.

Using routinely collected data, the evaluation will assess whether the reconfigurations were associated with changes in process, outcomes, and costs of care. Data will be collected retrospectively from 2004, up to the point at which services began to change; while ‘after’ data will be collected from the points at which the new models were fully in place, through to December 2013.

Care process measures have been selected for the evidence indicating relevance to quality of care and their positive association with improved outcomes
[28-30]. Measures include proportion of patients appropriately receiving thrombolysis, admitted to a stroke unit for 50% of their stay, appropriately receiving aspirin in the acute period, assessed by a multidisciplinary team, and receiving a swallowing test within the first 24 hours of care. These data will be drawn from national data sources (the Royal College of Physicians’ Sentinel Stroke Audit, the Stroke Improvement National Audit Programme (SINAP), and the Sentinel Stroke National Audit Programme (SSNAP)).

Outcome measures will include patient’s length of hospital stay, discharge destination, readmission rates, and mortality (in hospital, at 30 days, and at one year); these data will be drawn from HES and ONS datasets. Patient’s independent function (measured through Barthel Index score at discharge, and/or Modified Rankin score) will be drawn from Sentinel audit data, SINAP and SSNAP.

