### Analysis of outcomes

#### Econometric analysis

The outcome variables measured at the Trust level in each time period will be regressed against the covariates, with particular interest in interactions showing the impact of region following the introduction of stroke service reconfigurations. The regression model is:

$$y_{\mathrm{it}}=\alpha_{0}+\alpha_{1}A_{i}+\alpha_{2}Y_{t}+\alpha_{3}R_{\mathrm{it}}+\alpha_{4}X_{\mathrm{it}}+e_{\mathrm{it}}$$

where *y* is the outcome of interest (mortality, LOS), *i* indicates Trust, *t* indicates year, *A* is region, *Y* is year, *R* is an indicator variable taking the value one if stroke services in Trust *i* in each region *A* in year *t* have been reconfigured (1 = yes, 0 otherwise), *X* is a set of patient and Trust characteristics, the αs are coefficients to be estimated, and *e* is an error term. The regression model used will depend on the nature of the dependent variable. Of particular interest are the sign and statistical significance of the coefficient α_*3*_. If for reconfigurations in London or Greater Manchester α_*3*_ indicates a favourable result, i.e. a reduction in mortality and/or on LOS, the following cost-effectiveness analysis will be undertaken.

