First, the reconfigurations took place at slightly different times, and took different trajectories, with Greater Manchester taking a more phased approach than occurred in London. Therefore, as the reconfigurations have different ‘before’ and ‘after’ phases, it is possible that external factors—such as participation in national audits—might have influenced the two reconfigurations differently. Also, conclusions drawn about the relationship between reconfiguration and any improvements seen are less clear in ‘before’ and ‘after’ studies. It is possible that any improvements that occur could have occurred anyway and not as a direct result of the policies implemented. Without any randomisation, it is also harder to rule out potential biases and gaming, such as admitting less complex patients. However, these complexities reflect the ‘real world’ nature of service reconfiguration, and change more broadly, and are thus likely to be faced quite commonly in evaluations of this kind. As our research design actively seeks to analyse such contextual influences, this in fact represents an opportunity to improve understanding of the relationship between national (‘macro’) drivers for improvement and organisational (‘meso’) responses to these.

The retrospective nature of this evaluation impacts on the qualitative component of the research. For example, planning and implementation events could not be observed; in addition, interviewees’ recollection of events will naturally vary. Ensuring suitable representation of stakeholders—based on documentary analysis—and applying Patton’s validity criteria
[35] in the analysis will be key to ensuring that important lessons are not missed. In terms of studying patient experience, only patients who have recently experienced reconfigured services will be interviewed, so that no ‘before’ equivalent will be available. However, we will compare these patient experience data with literature on the experiences of stroke patients and carers
[36,37], so that the analysis can examine whether patients’ concerns have been addressed by changes brought about by the reconfigurations.

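### A single on/off indicator averages all post-reconfiguration years, so the model cannot show whether an effect lasted and can mix service age into the London–Manchester comparison

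*Protocol article*

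**What the plan says.** Econometric analysis prints a regression of Trust-by-year outcomes on region, year, R and other characteristics. R "is an indicator variable taking the value one if stroke services in Trust" i have been reconfigured in year t, and zero otherwise. Inference is tied to one term: "Of particular interest are the sign and statistical significance of the coefficient" α3. The lead-in sentence announces a model "with particular interest in interactions showing the impact of region following the introduction of stroke service reconfigurations", but the printed equation contains no interaction. The same model is reused for functional independence and for process measures.

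Data collection (Understanding what works and at what cost) sets the windows. For the before period: "Data will be collected retrospectively from 2004, up to the point at which services began to change". For the after period: "data will be collected from the points at which the new models were fully in place, through to December 2013". The start is therefore specific to each region and the end is common.

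The Discussion says that "the reconfigurations took place at slightly different times, and took different trajectories, with Greater Manchester taking a more phased approach than occurred in London", and accepts that the before and after phases differ. It treats this as a matter of exposure to outside influences such as national audits, not of how long each service had been running.

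Objective 1 is "To identify the barriers and facilitators for major system reconfiguration, implementation, and sustainability". Research question 5 asks whether London's extra investment bought better outcomes than Greater Manchester's smaller one.

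**The concern.** A 0/1 indicator with one coefficient gives the average effect over whatever post-years are in the data. It says nothing about the path within them. A benefit that had gone by 2013 and one that was still building can produce the same α3.

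The averaging also matters between regions. If one region contributes more post-years than the other, and the effect depends on time since full implementation, the two averages are taken at different service ages. Splitting α3 by region does not remove this, because each regional coefficient is still an average over its own span. Research question 5 could then credit the London model or its funding with a difference that comes from age alone.

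Two further uses depend on the same number. A favourable α3 opens the cost-effectiveness analysis. The quantitative findings are also fed into the phase-two interviews, which cover longer-term impact (Interviews; Data synthesis). In both places a single average may hide the trend that matters.

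**Working it through.** The article gives no sample size, power or expected effect for this regression, so there is no planned figure to reproduce. The check is structural: noise-free annual data for 2004 to 2013, fitted by least squares with region and year terms and R coded 0/1.

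**Inputs from the document.** Binary R (Econometric analysis); data from 2004 to December 2013 (Data collection); London model implemented in 2010, month not given (Analysis of cost-effectiveness).

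**Assumptions.** Greater Manchester start varied from 2009 to 2012, because no date is given; whole-year steps with no transition gap removed; weights of 24 London, 10 Greater Manchester and 120 rest-of-England units; effects in arbitrary units, negative meaning benefit.

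**Step 1: can the coefficient tell paths apart?** Four post-years, 2010 to 2013:

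- Sustained: (−1.00 − 1.00 − 1.00 − 1.00)/4 = −1.00
- Fading: (−1.75 − 1.25 − 0.75 − 0.25)/4 = −1.00
- Growing: (−0.25 − 0.75 − 1.25 − 1.75)/4 = −1.00

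The fitted coefficient was −1.00 in all three cases.

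**Step 2: same path by age in both regions, different starts, R split by region.** Let the effect k years after the start be −(0.5 + g·k), with k = 0, 1, 2 and so on. The mean over n post-years is −(0.5 + g(n − 1)/2). The London minus Manchester difference is therefore about −g(n_L − n_M)/2, although the true difference at equal age is zero. London has n_L = 4.

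| Manchester start | n_M | g = 0.1: formula / fitted | g = 0.25: formula / fitted | g = 0.5: formula / fitted |
|---|---|---|---|---|
| 2009 | 5 | +0.050 / +0.056 | +0.125 / +0.139 | +0.250 / +0.278 |
| 2010 | 4 | 0 / 0 | 0 / 0 | 0 / 0 |
| 2011 | 3 | −0.050 / −0.061 | −0.125 / −0.153 | −0.250 / −0.307 |
| 2012 | 2 | −0.100 / −0.120 | −0.250 / −0.300 | −0.500 / −0.601 |

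Example, g = 0.5 and a 2011 start: London −(0.5 + 0.5 × 1.5) = −1.25; Manchester −(0.5 + 0.5 × 1) = −1.00; difference −0.25. The fitted values were −1.247 and −0.940, difference −0.307. The fit is somewhat larger than the formula because the shared year terms absorb part of the changing effect in the other reconfigured region.

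**Step 3: constant effect of −1.** With Manchester starting in 2009, 2011 or 2012, both regional coefficients were −1.00, so the false difference is 0.

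**Step 4: single R exactly as printed.** With true effects of −1 in London and 0 in Manchester and a common start, α3 = (24 × −1 + 10 × 0)/34 = −0.71. With Manchester one year later the fit gave −0.73. The regional contrast is not estimated at all until R is split by region.

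**The case against.** The strongest reply is that the regression is being faulted for a task it was never given. Objective 1 concerns what hinders and helps sustainability, and the protocol assigns that to its implementation-and-sustainability strand. The quantitative strand is asked whether improvements were delivered, and an average post-implementation effect answers that. This stands. A reader might infer that the model contradicts the sustainability objective, or that the objective is left to interviewees' memory. The documents support neither. The Documentary analysis section collects records throughout the study because of the interest in sustainability, and staff are interviewed in two phases. What remains is that the numbers passed to that strand carry no information on persistence.

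Second, the maturity problem is conditional. It vanishes for a constant effect, the Discussion calls the timings only slightly different, and starting the after window at full implementation excludes the roll-out, where bedding-in would be expected to be strongest. All of this is right and rules out saying that research question 5 is confounded. It does not dispose of the point: change after full implementation is still averaged, and the printed model offers no way to check whether the effect is constant.

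Third, this is a condensed article, its text mentions interactions, and further terms could sit in a full analysis plan. That is fair as to the data: outcomes are indexed by Trust and year, so the limit belongs to the printed equation and not to what the study could show. But the exposure term and the coefficient to be read are stated choices, and the announced region interaction would separate London from Manchester without separating early from late years.

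**Conclusion.** The point holds in a limited form. As printed, the model cannot distinguish a sustained effect from a fading or growing one; that follows from the 0/1 coding and needs no assumption about the data. The London–Manchester contrast can be confounded with service maturity, even with region-specific R, if the effect changes with time since full implementation and the start dates differ.

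Under assumed growth of 0.1 to 0.5 units per year, a one-year gap produced a false difference of about 0.06 to 0.31 units and a two-year gap about 0.12 to 0.60. These figures illustrate the mechanism. They do not estimate the bias in this study: with no Greater Manchester date, neither size nor sign can be derived, and the bias is zero for constant effects or coincident starts. A reader might conclude that the regional comparison is already invalid; the documents do not show that. This is a worthwhile and inexpensive improvement to the specification, which would strengthen the quantitative evidence that the case studies and phase-two interviews draw on.

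**What to change.** - Keep the 0/1 estimate as the overall effect.
- Let R differ by region, so that the printed equation matches the interactions announced in the text and research question 5 is actually estimated.
- State the date of full implementation used for each region, and add indicators for time since that date (for example year 1, year 2, year 3 and later) in each region. Report these as the quantitative evidence on persistence.
- Report the research question 5 contrast at equal time since full implementation, over the longest span that both regions reach by December 2013, beside the pooled contrast.
- Note that Greater Manchester's phased roll-out makes this alignment approximate, since some Trusts there may have been working under the new arrangements before the region's model was complete.

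The cost is a few extra regression terms on data already to be collected. Year-specific estimates will be less precise than the pooled average, and the equal-time contrast leaves out some post-years from the earlier region. That is why the pooled results should stay alongside.

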## Background

Significant changes in provision of clinical care within the English National Health Service (NHS) have been discussed in recent years, with the proposal to concentrate specialist services, such as major trauma, cardiac surgery, and specialist paediatrics, in fewer centres
[1,2]. Such ‘reconfigurations’ have been defined as, ‘a deliberately induced change of some significance in the distribution of medical, surgical, diagnostic and ancillary specialties that are available in each hospital or other secondary or tertiary acute care unit in locality, region or healthcare administrative area’
[3].

Stroke is a major public health issue, accounting for over 10% of deaths in England and Wales, and much disability among stroke survivors
[4,5]. Evidence indicated variations in quality of acute stroke care, as well as in services provided for the management of Transient Ischaemic Attack, rehabilitation, and life after stroke, with many patients not receiving evidence-based treatments
[5,6]. The Department of Health’s National Stroke Strategy recommended major system change for stroke
[4]. Recognising the need to improve stroke care at a system-wide level, London and Manchester led the way in this process. Other parts of the English NHS are now also seeking to reconfigure their stroke services
[7].

Research has highlighted challenges in carrying out acute service reconfiguration
[3,8,9], as has previous research on mergers of healthcare providers
[10], particularly where there is resistance from professionals and the public
[11]. Other research has highlighted challenges of major system change at local level
[12]. This evaluation builds on previous research by studying the processes and outcomes of implementing system reconfigurations of acute stroke care in different contexts (London and Greater Manchester) and using different models. It also provides an opportunity to investigate health economic arguments about whether greater investment in acute stroke services might result in savings to the system overall
[13].

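### The outcome model assumes one time effect for London, Greater Manchester and the rest of England, in whole years, and plans no check of that assumption although data from 2004 allow one

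*Protocol article*

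**What the plan says.** The Econometric analysis section of the protocol article prints the model as an equation. The unit is the Trust in a time period: "The outcome variables measured at the Trust level in each time period will be regressed against the covariates". The subscripts and terms are defined so that "t* indicates year, *A* is region, *Y* is year". R is 1 for a Trust and year in which stroke services "have been reconfigured (1 = yes, 0 otherwise". The year term carries no regional subscript, and region is not interacted with time.

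The coefficient on R has two uses. It is the quantity to be interpreted ("Of particular interest are the sign and statistical significance of the coefficient" α3), and it is a gate: if it "indicates a favourable result, i.e. a reduction in mortality and/or on LOS, the following cost-effectiveness analysis will be undertaken". The sections on functional independence and on process changes apply the same model to their own measures.

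On timing, the Data collection section says "Data will be collected retrospectively from 2004, up to the point at which services began to change", and that collection resumes once the new models are fully in place and runs to December 2013. The cost-effectiveness section dates the London model to 2010. The Discussion says the two changes followed different courses, "with Greater Manchester taking a more phased approach than occurred in London". The Design section names the rest of England as the wider comparator, while the Background notes that "Other parts of the English NHS are now also seeking to reconfigure their stroke services".

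**The concern.** A controlled before-and-after comparison attributes to the intervention whatever change in the treated regions is not matched in the comparator. That is sound only if the regions would otherwise have moved in parallel. The printed model imposes parallel movement, apart from what the covariates explain, and nothing in the article says it will be examined.

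The Discussion concedes that improvement might have happened anyway and that outside influences might have touched the two regions differently. Its answer is to study context, not to change or test the regression. Yet several years of pre-change data will be held.

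A false favourable α3 would start an economic evaluation of an effect that is not there, and a false null would withhold one. The value-for-money question and the London versus Manchester question both depend on this, and the assumption carries over to the process and functional analyses.

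The yearly time unit is a smaller, related matter. Collection starts and stops at actual points of change, which may fall within a year, and a whole-year 0/1 step cannot follow them.

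**Working it through.** The article gives no effect size, variance or power figure for this analysis, so there is no stated number to reproduce. The check asks what the printed equation returns when its trend assumption fails.

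**Inputs from the article.** Series 2004 to December 2013; London change in 2010; transition left out of collection; year effect common to all regions; R a 0/1 step.

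**Assumptions.** The whole of 2010 is the omitted transition. The treated-minus-comparator difference drifts linearly by δ a year. The true effect is τ. For the fitted runs there are 30 treated and 120 comparator Trusts.

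**Bias from a differential trend.** With a dummy for each year, α3 is the after-mean minus the before-mean of the treated-minus-comparator difference.

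- Mean of 2004–2009 = 2006.5
- Mean of 2011–2013 = 2012.0
- α3 = τ + δ × (2012.0 − 2006.5) = τ + 5.5δ

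Fitting the printed equation to noise-free data confirms 5.5δ. Entering year as one linear term gives 5.2δ. Counting 2010 as an after-year gives (2011.5 − 2006.5)δ = 5.0δ.

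For one treated region against the comparator, the multiplier does not depend on where the break falls. Number the ten years 0 to 9, with n years before and k whole years omitted. The before-mean is (n − 1)/2 and the after-mean is (n + k + 9)/2, so the gap is (10 + k)/2: 5.0, 5.5 and 6.0 for k = 0, 1 and 2. So it also holds for Greater Manchester, whose dates are not given.

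**Size with τ = 0:**

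| Assumed δ (percentage points a year) | Spurious α3 (5.5δ) |
|---|---|
| -0.1 | -0.55 |
| -0.2 | -1.10 |
| -0.3 | -1.65 |

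A positive δ would hide a true benefit by the same amounts.

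**What a region-specific linear trend buys.** Adding it brings the linear bias to 0. The standard error of α3 rises by a factor of 2.03 under independent errors. If the differential drift is curved, say 0.01t² with t in years from 2004, the model without the trend is biased by 0.01 × (64.67 − 9.17) = 0.555, and the model with it still by 0.22. The trend term is therefore a check with a price.

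**The case against.** The strongest reply is that a shared time effect is the ordinary difference-in-differences specification. On that view the printed equation is a base model in a condensed article, and robustness runs belong in a fuller plan that is not shown. The article also says the regression form will depend on the outcome. It is right that this is no algebraic error, and that nothing in the document shows the regions were diverging. But the equation is printed in full, the gate on α3 is stated, and the threat is acknowledged without an analytic response. A check on data the study will hold is a concrete improvement on the stated method.

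Three stronger readings are tempting and not supported.

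- **Miscoding of 2010.** A reader might infer that the yearly step dilutes the London effect: if a half-exposed 2010 counted as after, α3 would be 0.875τ. The Data collection section leaves the transition out, and with it omitted α3 is 1.00τ. R is also indexed by Trust and year, so it can carry phasing across years. Only part-years and phasing within a year remain, and the article gives no figure for them.
- **Comparator contamination.** A reader might infer that the rest of England is itself reconfigured and that α3 shrinks in proportion. The Background says only that other areas are seeking change, with no share or dates. The definition of R is not confined to the two regions, so a changed comparator Trust could be coded 1. With an equal effect there is then no dilution, though α3 would no longer refer only to the London and Greater Manchester models. If 10% of comparators (assumed) changed and were coded 0, the loss would be 3% for change from 2013 and 10% for change from 2011.
- **A complete cure.** A reader might infer that data from 2004 could remove every such problem. They allow a test of pre-trends and an adjustment for a linear difference. They do not correct curved trends, shocks that coincide with the change, or dilution.

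Nor does α3 settle the whole study: the research questions on the process of change and on stakeholders' views rest largely on qualitative work.

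**Conclusion.** The point holds as an untested assumption with real leverage. The printed model forces a common time effect, works in whole years, and gates the economic analysis on α3 without any look at pre-change trends. A linear differential trend enters α3 multiplied by about 5.5 (5.0 to 5.5 across the fitted codings of year and of 2010). The spurious -0.55 to -1.65 points rests on an assumed δ of -0.1 to -0.3 points a year. The multiplier rests on the stated dates and an assumed one-year omission; the size of δ is unknown. The document supports no figure for dilution, either from transition coding or from reconfigured comparators. The matter should be put right before the outcome analysis, as an addition to the plan and not as the repair of a wrong formula.

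**What to change.** - Keep the stated model as primary, but take calendar quarter as t where the source data are dated, so that the cut-points in the Data collection section are honoured within a year.
- Estimate pre-period leads separately for London and Greater Manchester against the rest of England, from 2004 to each region's start of change, and report them beside α3.
- Report α3 with and without region-specific linear trends, the latter model being primary and the former a sensitivity analysis.
- As a further sensitivity analysis, censor from its own change date any comparator Trust that centralises stroke services before December 2013, so that α3 refers only to the London and Greater Manchester models. This needs those change dates to be found.

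The cost is re-aggregation of dated records, extra model runs, and about a doubling of the standard error of α3 in the region-trend analysis (independent errors). None of this protects against non-linear differential trends or events that coincide with the change, and the report should say so.

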## Design/methods

### Design

#### Understanding what works and at what cost

Identifying what process and outcome changes have occurred, and at what cost, provides evidence about the extent to which the reconfigurations have succeeded in their objectives of changing the system of service provision and quality of care. This component of the evaluation will analyse documentary evidence to establish the models applied in London and Greater Manchester; it will also identify whether any changes in process and outcomes can be associated with these changes.

In assessing the nature and results of the two reconfigurations, the evaluation will apply a controlled before-and-after design
[24]. This will compare the London and Manchester models in terms of the impact they had on processes, outcomes, and costs of care. In addition to comparing London with Greater Manchester pre- and post-reconfiguration, the analysis will make a wider comparison with the rest of England. This approach will permit observed changes to be analysed in the context of changes that take place in the rest of England over this period. A two-step approach will be taken to the analysis of outcomes: in the first instance, the impact of the reconfigurations on mortality and length of stay will be investigated; if evidence of impact on these is found, a more detailed cost-effectiveness analysis will be undertaken.

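### The claim of impact rests on the significance of α3 in a Trust-by-year model with one error term; treating Trust-years as independent can misstate its error in either direction, and Trust clustering alone may not be enough

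*Protocol article*

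**What the plan says.** The Econometric analysis section prints a single equation. Its data are described as "The outcome variables measured at the Trust level in each time period". The right-hand side has region, year, the indicator R, patient and Trust characteristics, and a term e that "is an error term. The regression model used will depend on the nature of the dependent variable". There is no Trust term and no region-by-year term. R equals one when stroke services in Trust i in year t "have been reconfigured (1 = yes, 0 otherwise").

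The result to be read off is stated as: "Of particular interest are the sign and statistical significance of the coefficient" α3. The next sentence gives the consequence: if α3 for London or Greater Manchester "indicates a favourable result, i.e. a reduction in mortality and/or on LOS, the following cost-effectiveness analysis will be undertaken". The Design section words the same step as "if evidence of impact on these is found, a more detailed cost-effectiveness analysis will be undertaken".

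Two regions were reconfigured, and "the analysis will make a wider comparison with the rest of England". The Discussion says that Greater Manchester's roll-out was more phased than London's. The sections on functional independence and on process changes reuse the same regression model.

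No significance level and no method for standard errors is named.

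**The concern.** About ten yearly values from one Trust are not ten independent observations. Two kinds of dependence matter here.

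- **Within Trust.** Stable differences between Trusts and year-to-year persistence both fall into e, because the model has a region term but no Trust term.
- **Within region and year.** Anything that moves all Trusts of a region together in some years (coding, audit participation, local policy) coincides with R and looks like an effect. The Discussion recognises this threat in substance: it says that outside factors may have affected the two reconfigurations differently, and that improvement might have come without them. Nothing in the printed model separates such a shock from α3.

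Research question 2 depends on α3 directly. The value-for-money questions depend on it through the cost-effectiveness stage. An error that is too small could launch that stage on regional drift; one that is too large could hide a real effect.

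**Working it through.** The article gives no sample size, variance, intraclass correlation (ICC) or significance level for this analysis, so there is no figure of its own to reproduce. The check is a simulation of the printed model with no effect present.

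**Inputs from the article:** data from 2004 to December 2013 (10 years); London model implemented in 2010; 10 Greater Manchester Trusts.

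**Assumed:** 24 London Trusts (the number of London Stroke Units, as a proxy); 110 other Trusts in 7 regions; Greater Manchester also switching in 2010; no covariates X; all correlation values. The model was OLS with region dummies, year dummies and a separate R for each region, tested two-sided at 5%, with 1,500 runs per scenario.

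**Results for the London coefficient:**

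| Dependence assumed | True SD | Mean default SE | Rejection, default SE | Rejection, Trust-clustered SE |
|---|---|---|---|---|
| None | 0.144 | 0.145 | 4.5% | 5.3% |
| Stable Trust effect, ICC 0.5 | 0.148 | 0.203 | 0.5% | 6.5% |
| Trust AR(1) 0.5 | 0.193 | 0.145 | 13.9% | 5.5% |
| ICC 0.5 plus AR(1) 0.5 | 0.191 | 0.202 | 4.4% | 5.8% |
| Region-year shocks, 2% of variance | 0.177 | 0.147 | 9.6% | 11.9% |
| Shocks, 5% | 0.219 | 0.148 | 18.8% | 20.4% |
| Shocks, 5%, autocorrelated 0.5 | 0.262 | 0.148 | 26.7% | 29.0% |
| Shocks, 10%, autocorrelated 0.5 | 0.345 | 0.150 | 40.9% | 42.8% |
| ICC 0.5, AR(1) 0.5 and 5% autocorrelated shocks | 0.350 | 0.206 | 25.1% | 28.4% |

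**Hand check.** With 6 years before and 4 after, residual variance 1 and independent errors, the variance of London's coefficient is

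(1/6 + 1/4) × (1/24 + 1/110) = 0.4167 × 0.05076 = 0.02115, so SE = 0.145. This agrees with the first row.

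Independent region-year shocks with variance τ² add about (1/6 + 1/4) × (1 + 1/7) × τ² = 0.476 τ². For a 5% share, τ = 0.2294 and τ² = 0.0526, so the addition is 0.0251. The total is 0.0462 and the true SD is 0.215 (simulated 0.219). A test that still uses 0.145 rejects with probability 2 × [1 − Φ(1.96 × 0.145/0.215)], about 18%, in line with the simulated 18.8%.

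**Why Trust clustering does not cure the shocks.** The added 0.476 τ² contains no count of London Trusts. It comes from having one London. Clustering on Trust treats the London Trusts as independent of each other, so with 5% shocks the mean clustered SE stays at 0.1435 against a true SD of 0.2187. The ratio is 0.66.

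**Limit of a placebo comparison.** If k untreated regions are each given the same start date and a treated region is ranked among them, the smallest one-sided p-value is 1/(k + 1). With k = 8 this is 1/9 ≈ 0.11; with the 7 regions assumed above it is 1/8 = 0.125. The article does not count the comparison regions.

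**The case against.** The strongest reply is that the article never says that independent-error standard errors will be used. It calls e an error term and lets the regression depend on the outcome type. The method for standard errors is commonly left to the full protocol or SAP, so its absence is not in itself a fault. That stands, and a reader should not infer that the plan has chosen default errors. What remains is that the article does fix the model terms, without a Trust effect, and does name significance as a criterion. The routine remedy that a SAP would be expected to supply, clustering on Trust, does not deal with regional shocks when only two regions are reconfigured.

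Three further objections also hold in part.

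- **The gate.** A reader might infer that statistical significance is the go/no-go rule. The gate sentence asks for a reduction and does not repeat significance. The link comes from the preceding sentence and from the Design section's demand for evidence of impact. It is a reasonable reading but not a stated rule.
- **The indicator.** R is indexed by Trust and year, and Greater Manchester was phased. Saying that treatment varies only by region and time would be too strict, though it is a fair approximation for London. Phasing does not remove shocks shared by Greater Manchester's Trusts.
- **The size.** The rates depend on correlations chosen for the simulation, which also omits X. They run from 0.5% to about 41% with default errors, and with both Trust-level components the distortions roughly cancel (4.4%). A reader might infer that false positives are certainly inflated; the document does not support that.

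**Conclusion.** The point holds in conditional form. The claim of impact is tied to inference on α3, and the printed model makes no allowance for repeated Trusts or for shocks shared within a region and year. Error bars that treat Trust-years as independent may be too wide, too narrow or about right, and the article gives no figure that would settle which.

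On the assumed inputs, Trust-level dependence alone moves a nominal 5% test to between 0.5% and 13.9%, and Trust clustering brings it back to about 5.5–6.5%. Region-by-year shocks of 2% to 10% of variance give about 10% to 41% with default errors, and about 12% to 43% after Trust clustering. The second result rests on shocks of that size existing, which is plausible but not shown. The reason that clustering fails, namely that only two regions are treated, is a feature of the design.

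A reader might conclude that a placebo ranking should replace the regression test. It cannot be the sole basis for the claim: with 8 comparison regions its p-value cannot fall below about 0.11.

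**What to change.** 1. Estimate a separate coefficient for London and for Greater Manchester. Add Trust effects to the model and/or use Trust-clustered standard errors, with a few-cluster correction for Greater Manchester's 10 Trusts. Apply the same to the functional-independence and process analyses that reuse the model.
2. State the inferential threshold for α3 that counts as evidence of impact, so that the Design and Econometric analysis sections describe one rule for moving to the cost-effectiveness stage.
3. Add a placebo analysis as a supporting check. Assign the same start date to each untreated English region in turn, and show where London and Greater Manchester fall in that spread. State the number of comparison regions and the smallest attainable p-value, and say how Greater Manchester's phased start is represented.
4. Temper the claim of impact if the placebo spread is comparable in size to the estimated effect.

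The cost is a few more lines of analysis on data that the study already plans to hold for the rest of England. The downside is wider or less favourable intervals for some outcomes.
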